### Procedure

Adolescents are informed about Move It Now by their youth health-care nurse or their medical specialist. When an adolescent decides to participate in Move It Now, he or she contacts the researcher by mail or e-mail. Thereafter, the researcher contacts the adolescent and one of the parents by telephone. In this phone call, the researcher checks the inclusion criteria, gives information, and asks the adolescent and the parent to send their signed informed consent forms.

When the researcher has received the signed informed consent forms, the adolescent and the parent are registered at the Move It Now website. An automatic e-mail with their login codes is sent to them. When the adolescent logs into the website, he or she first fills out the online questionnaires; the PedMIDAS, the self-constructed sleep questionnaire, the CHQ, the PCQ, the IBES, and the PCS-C. For logistic reasons, the EQ-5D-5L and a separate reply form are sent to the adolescent by e-mail. Additionally, the adolescent keeps an online Pain Dairy for one week. After this baseline measurement, the adolescent and the parent receive an automatic e-mail that informs them whether they can start with Move It Now directly in the intervention group or if they have to wait for seven weeks.

### Statistical analyses

Power calculations have shown that for an effect of d = .70 on the questionnaires, a sample size of 25 participants per group is needed (power 80%, alpha 0.05). Adjusting for potential study withdrawal (20%), we estimate that 60 participants should be included.

Multi-level modelling will be applied for longitudinal analysis. This analysis allows handling incomplete data with a minimal loss of information. Results of the measurements at baseline, post-treatment, and at three months follow-up will be presented. Linear splines will be used to test the differences in outcomes between time points. For all differences, effect sizes will be reported, with d = .2-.5 indicating a weak effect, d = .5-.8 indicating a medium effect and d = > .8 indicating a strong effect [38].

The EQ-5D-5L, in combination with the CHQ [29], will be used for the economic evaluation of Move It Now. The results will be expressed as cost per Quality Adjusted Life Year (QALY).

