## Methods intervention study

### Population

The study sample will consist of 60 adolescents. Adolescents are eligible to participate if they meet the following criteria: age 12 to 17 years; chronic pain for at least three months; abdominal pain, headache, back pain or limb pain; no apparent medical cause of pain (an exception is made for adolescents with migraine); withdrawing from activities or feeling overburdened; access to the Internet at home; fluent in the Dutch language; no current psychological treatment for pain; no severe psychosocial problems.

Recruitment of participants takes place via the referral study, the Internet, the media, and rehabilitation centers and hospitals in the Netherlands. The study started April 2009. The inclusion of patients will end in June 2012. The three-month follow-up period will be finished in September 2012.

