## Design

The intervention study is a randomized controlled trial. Participants are automatically randomly assigned to the experimental group or the waiting list group by the Move It Now website. The Move It Now website uses a randomization list which has been generated by an independent statistician. Block randomization has been used to keep the group sizes equal. Prior to entry of the participants into the study, both the researchers and the therapist are blinded for randomization. Figure 1 shows the design and the anticipated flow of participants.

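### The stated inputs do not give 25 per group on the usual two-sided, unadjusted reading (33–34 are needed), and the 20% withdrawal allowance is multiplied on rather than divided out

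*Protocol article*

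**What the plan says.** The sample-size justification is two sentences in the protocol article, under Statistical analyses in the intervention-study methods. The target is set "for an effect of d = .70 on the questionnaires", and the result is that "a sample size of 25 participants per group is needed (power 80%, alpha 0.05". The next sentence reads: "Adjusting for potential study withdrawal (20%), we estimate that 60 participants should be included". The Population section repeats the total: "The study sample will consist of 60 adolescents".

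Two other statements matter here. Allocation is equal, since the Design section says "Block randomization has been used to keep the group sizes equal". The planned analysis includes the baseline measurement: "Multi-level modelling will be applied for longitudinal analysis", and of that analysis the article says "This analysis allows handling incomplete data with a minimal loss of information".

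The article does not say whether alpha is one- or two-sided, which test the calculation assumed, or whether a baseline correlation entered it.

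**The concern.** An effect size, a power, an alpha and two equal groups are enough to recompute an unadjusted sample size. An alpha of 0.05 without qualification is normally taken as two-sided. On that reading 25 per group is too few for 80% power at d = .70. The withdrawal step also looks wrong, because adding 20% to a target does not make up for losing 20% of those enrolled.

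This is the article's only justification of the sample size. If the stated 80% is not what the design delivers, a null result could be taken as stronger evidence against an effect of d = .70 than it is. On the two-sided unadjusted reading the trial would miss a true effect of that size about one time in three.

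**Working it through.** **Inputs, all from the protocol article.** d = 0.70, power 80%, alpha 0.05, 25 per group, withdrawal 20%, 60 in total (Statistical analyses; the total also in Population); equal allocation (Design). Sidedness, test and baseline correlation are not given, so each is varied below.

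**1. Where 25 can come from, unadjusted.** The normal approximation per group is n = 2(z_alpha + z_power)² / d², with z_power = 0.842 and d² = 0.49.
- One-sided: 2(1.645 + 0.842)² / 0.49 = 25.2. The t-test gives 25.9. Both round up to 26, so 25 is matched approximately.
- Two-sided: 2(1.960 + 0.842)² / 0.49 = 32.0, just above 32 unrounded (32.04), so 33. The t-test gives 33.02, so 34. Neither matches 25.

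**2. Where 25 can come from, baseline-adjusted.** Adjusting for a baseline with correlation r multiplies the variance by 1 − r². The correlation is an assumption, as the article gives none. At r = 0.5, two-sided, the t-based calculation gives n = 25.02 and power 80.0% at 25 per group. The normal approximation reaches 25 at r of about 0.47, from r = √(1 − 25/32.04).

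**3. The withdrawal step.**
- The stated total is 2 × 25 = 50, then 50 × 1.20 = 60.
- To keep 50 after a 20% loss: 50 / 0.80 = 62.5, so 63 (64 with equal arms).
- What 60 leaves after a 20% loss: 60 × 0.80 = 48, or 24 per group, one fewer per group than the stated 25.
- Loss that 60 can absorb while keeping 50: 1 − 50/60 = 16.7%.

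**4. Power for d = 0.70 (t-based).**

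| Test | 25 per group | 24 per group |
|---|---|---|
| Two-sided, unadjusted | 67.9% | 66.1% |
| One-sided, unadjusted | 78.7% | 77.2% |
| Two-sided, assumed r = 0.3 | 72% | 70% |
| Two-sided, assumed r = 0.4 | 75% | 74% |
| Two-sided, assumed r = 0.5 | 80% | 78% |
| Two-sided, assumed r = 0.6 | 86% | 84% |

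With no withdrawal at all (30 per group), the two-sided unadjusted test has 76% power. The d detectable with 80% power, two-sided and unadjusted, is 0.81 at 25 per group and 0.83 at 24.

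**5. Relative weight of the two problems.** On the two-sided unadjusted reading, the gap from 80% to 67.9% (12.1 points) comes from using 25 instead of 33–34. The withdrawal slip adds 67.9 − 66.1 = 1.8 points.

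**The case against.** A reader might infer that 25 can only be a one-sided figure, and that the trial therefore has 66–68% power. The documents do not support either statement. A two-sided calculation adjusted for baseline with r of about 0.5 also gives 25, and the planned analysis is a longitudinal model that includes baseline. The 66–68% needs both a two-sided alpha and an unadjusted comparison, and the article states neither. Over the readings tried, power at 24 per group runs from 66% to 84%, so quoting only the lowest figure would mislead. The Discussion also states directional hypotheses, which would fit a one-sided calculation, although they do not declare one. This much of the objection stands.

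It does not rescue the paragraph. The assumed correlations show that 80% is reachable, not that it was planned for, since the article gives no correlation. On the two readings that produce about 25 (one-sided, or two-sided with r about 0.5), 24 completers per group give 77% and 78%, still short of 80%.

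A second argument is that a multilevel model uses incomplete records, so withdrawal costs less than a head count suggests. That helps for participants with some later data. It does little for those lost before any post-baseline measurement, and the article itself chose to allow for withdrawal.

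A third is that an article condenses a fuller protocol, where sidedness and test may be recorded. That excuses an omission. It does not excuse printed figures that do not agree: 60 less 20% is 48, not 50, on any reading.

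**Conclusion.** The point holds in a conditional form. With the inputs as printed and the usual two-sided, unadjusted reading, 25 per group is wrong: 33–34 are needed, and 24–25 completers per group give 66–68% power. This rests on two assumptions that the article does not state, namely that alpha is two-sided and that the calculation ignored baseline. If the calculation was one-sided, power at 24 per group is 77%. If it was two-sided with baseline adjustment, power is about 70%, 74%, 78% and 84% for assumed r = 0.3, 0.4, 0.5 and 0.6. It is therefore not shown that the trial is underpowered under its planned model; what is shown is that the stated 80% cannot be verified from what is printed.

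The withdrawal error depends on none of these assumptions. It is minor: two completers and about 2 power points. It should not be given equal weight as a cause of any shortfall.

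**What to change.** Keep 60 and rewrite the sample-size paragraph so that it states:
- whether alpha is one- or two-sided, the test assumed, and any baseline correlation behind the 25;
- 48 expected completers (24 per group) from 60 enrolled at 20% withdrawal, in place of the implied 50;
- the resulting power. Two-sided and unadjusted, this is 66% for d = .70, with 80% power for d = 0.83. If the planned baseline-adjusted analysis is the basis, give the power at the stated r (for example 78% at 24 per group if r = 0.5), with the reason for that r.

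The cost is one reworded paragraph and a less favourable power statement. No extra participants are needed, and design and analysis are unchanged. Holding 80% power at d = .70 two-sided and unadjusted would instead take 66/0.8 = 82.5 to 68/0.8 = 85 enrolled, i.e. 83–85 (84–86 with equal arms). Restating the figures avoids that.

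### Free improvement: estimate the seven-week between-arm contrast with one common baseline mean (or baseline as covariate), since the stated test reads as a less efficient change contrast

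*Protocol article*

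**What the plan says.** All of this stands in the protocol article; no SAP is at hand.

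- *Statistical analyses* names the model: "Multi-level modelling will be applied for longitudinal analysis". It lists what is reported: "Results of the measurements at baseline, post-treatment, and at three months follow-up will be presented". It then names the test: "Linear splines will be used to test the differences in outcomes between time points".
- The same section sizes the trial for a standardised effect of .70: "a sample size of 25 participants per group is needed", at "power 80%, alpha 0.05". It does not say whether alpha is one- or two-sided, and it gives no correlation between baseline and later scores.
- *Design* describes automatic allocation from an independent statistician's list: "Block randomization has been used to keep the group sizes equal". The waiting-list arm is assessed again after seven weeks, before it starts the intervention.
- *Procedure* (intervention study) has each adolescent complete the baseline measurement before an e-mail discloses the allocation.
- *Discussion* concedes that no control group remains at follow-up.

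The article does not say whether baseline has separate means per arm, one shared mean, or the role of a covariate.

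**The concern.** The quantity named for testing is a difference between occasions, and baseline is the only occasion before treatment. A spline running over baseline, post-treatment and follow-up has baseline as a modelled response. If each arm has its own baseline mean, the between-arm test of the first segment is a comparison of mean changes.

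That comparison is valid but uses baseline inefficiently. At r = 0.5 it does no better than ignoring baseline, and below 0.5 it does worse. It also over-corrects chance imbalance. If the arms differ at baseline by D, the change contrast is displaced by -(1-r)D given that difference. With 25 per group the standard error of D is sqrt(2/25) = 0.28 SD. An imbalance of one standard error therefore moves the estimate by 0.5 × 0.28 = 0.14 SD at r = 0.5, against a planned effect of 0.70.

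The seven-week comparison is the only randomised contrast this trial offers, so its precision matters.

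**Working it through.** **Inputs from the article:** d = .70, 25 per group, power 80%, alpha 0.05, 20% withdrawal, 60 randomised in equal groups.

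**Assumptions:** r is varied because no value is given. The test is taken as two-sided. d is in raw-score SD units. The SD is the same at both occasions and in both arms.

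**Step 1. The plan's own figure.** n per group = 2(z_alpha + z_beta)²/d².

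- One-sided 0.05: 2(1.645 + 0.842)²/0.49 = 25.2, so 26. Power at 25 per group is 79.7% (normal) or 78.7% (t). This reproduces the stated 25 to within one participant.
- Two-sided 0.05: 2(1.960 + 0.842)²/0.49 = 32.0, so 33 (34 by t). Power at 25 per group is 69.7% (normal) or 67.9% (t).

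Both figures are for comparing seven-week scores and ignoring baseline.

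**Step 2. Variance of the between-arm contrast, per person, in units of the score variance.**

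- Seven-week score only: 1
- Change contrast (separate baseline means): 2(1-r)
- Common baseline mean, or baseline as covariate: 1-r²

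The ratio of the third to the second is (1-r)(1+r)/[2(1-r)] = (1+r)/2, which never exceeds 1.

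**Step 3. Power, t-test, two-sided 0.05, 25 per group.** The effective effect is .70 divided by the square root of the variance.

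| r | Effective d, change | Effective d, common baseline | Power, change | Power, common baseline | Variance reduction |
|---|---|---|---|---|---|
| 0.3 | .70/√1.40 = 0.592 | .70/√0.91 = 0.734 | 53.6% | 72.0% | 35% |
| 0.5 | .70/√1.00 = 0.700 | .70/√0.75 = 0.808 | 67.9% | 80.0% | 25% |
| 0.7 | .70/√0.60 = 0.904 | .70/√0.51 = 0.980 | 87.9% | 92.4% | 15% |

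**Step 4. Where the choice settles the 80% question.** At 25 per group the common-baseline model reaches 80% at r of about 0.50 and the change contrast at about 0.63. At 24 per group the values are about 0.53 and 0.64.

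**Step 5. Allowing for withdrawal.** With 30 randomised and 24 completing per arm, everyone kept in the mixed model and a normal approximation, power goes from 56.6% to 72.0% (r = 0.3), 70.1% to 80.0% (r = 0.5) and 88.8% to 92.4% (r = 0.7).

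**Step 6. If the test is one-sided.** At 25 per group (t), power goes from 66.2% to 81.9%, 78.7% to 87.9% and 93.4% to 96.2%. The variance ratio is unaffected by sidedness.

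**The case against.** **The article does not specify separate baseline means.** A reader might infer from the wording that the plan has chosen to treat baseline as just another outcome with its own mean in each arm. The article does not say so. A spline model with a shared starting point and arm-specific slopes also fits the text, and an article may leave such detail to the full protocol or SAP. This stands as a limit: the change contrast is the natural reading, not a declared choice. What remains is that the article does name the test, as a difference between occasions, and gives no sign of baseline adjustment.

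**Both models are valid.** Under randomisation the change contrast is unbiased and keeps its type I error. This stands too. The point is one of efficiency, and of bias conditional on chance imbalance.

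**The power shortfall belongs to another question.** The 68% at 25 per group (66% at 24) is the two-sided power of a seven-week score comparison, and it is a shortfall only if the test is two-sided. One-sided, the stated sample size gives about 79%. A reader might infer that a common baseline mean recovers most of the missing power, or decides whether 80% is attainable. The documents support neither as a general statement, because they give neither r nor sidedness. Under a two-sided test the choice decides the matter only for r of roughly 0.50 to 0.63. At 0.3 both versions fall short, and at 0.7 both exceed 80%.

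**ANCOVA and the mixed model differ when scores are missing.** With 20% withdrawal planned for, a complete-case ANCOVA drops participants whom the multi-level model retains. This is a reason to put the constraint inside the model already planned.

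**Conclusion.** The point holds as a free improvement to the analysis, not as an error in the plan. As written, the test reads most naturally as a change contrast. Randomisation, with baseline taken before allocation is disclosed, makes a common baseline mean legitimate. The variance of the seven-week contrast then falls by the factor (1+r)/2 and, apart from a degree of freedom, never rises.

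The power gain is about 18, 12 and 5 percentage points at r = 0.3, 0.5 and 0.7 (72.0 - 53.6, 80.0 - 67.9, 92.4 - 87.9). This rests on a two-sided 0.05 test, d = .70 in raw-score SD units, equal SDs and 25 per group. The direction of the gain does not depend on sidedness; its size depends on r.

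Nothing is gained for the three-month follow-up, where both arms will have been offered the intervention. Nor does the change alter the allowance for withdrawal or settle the sidedness of the sample-size calculation.

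**What to change.** In *Statistical analyses*, state that:

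1. the between-arm contrast is taken at the end of the seven-week waiting period, comparing the waiting-list arm's assessment at that point with the experimental arm's post-treatment assessment;
2. it is estimated in the multi-level model with one common baseline mean for both arms (no group effect at baseline), or with baseline as a covariate, and participants with a missing post score stay in the mixed model;
3. the test is one- or two-sided, as intended, with the correlation assumed if the power statement is to rely on baseline adjustment.

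Three-month results should be reported separately, as changes without a concurrent control. The cost is a few lines of text. No participants, assessments or new data are needed, and the only statistical price is the degree of freedom spent on baseline. The choice should be fixed before outcome data are examined by arm.

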## Discussion

The primary aim of our study is to improve signaling, referral, and treatment of adolescents with chronic pain. In the referral study we will explore if the Pain Barometer, the signaling and referral instrument, is feasible in the context of preventive Youth Health-Care. In the intervention study we will explore if Move It Now, the guided self-help program via Internet, is efficacious.

Our study is the first in developing an instrument to signal chronic pain in adolescents that directly can be applied in practice. We expect the Pain Barometer to be a feasible instrument. A limitation of the referral study is that it is not possible to explore the validity of the Pain Barometer in this setting.

Move It Now is one the first tailored and guided self-help interventions via the Internet for adolescents with chronic pain. We expect the participants to cope with their pain more actively directly after the Move It Now intervention. We also hypothesize that Move It Now reduces pain frequency, pain duration, pain intensity, and pain disability. A strength of the intervention study is that it includes important but often neglected, outcome variables, i.e. coping with pain and quality of life. Additionally, the intervention is not only directed at the adolescents, but also at the parents. A limitation of the intervention study is that there will be no control group at follow-up, since the intervention is offered to the adolescents after a short waiting period. Furthermore, a waiting list group is used as a control. Therefore it will not be clear if the specific or nonspecific factors, such as attention, influence the intervention.

If the Pain Barometer appears to be feasible, it can be used to signal and refer adolescents with chronic pain at an early stage in various health care settings. If Move It Now is proved to be efficacious it can be easily implemented throughout the Netherlands, as the intervention is internet based. Then it will also be possible to perform a large scale (cost-)effectiveness study to examine the effect of Move It Now in daily practice. Additionally, future research should examine which elements are working for which adolescents. The Move It Now intervention could also easily be adapted to suit the needs of adolescents with other chronic health issues.

## Abbreviation

CBT, Cognitive-behavioral therapy; CHQ, Child health questionnaire; ECD, Electronic child dossier; EQ-5D-5L, EQ-5D-5L developed by the EuroQol Group; IASP, International association for the study of pain; IBES, Illness behaviour encouragement scale; PedIMMPACT, Pediatric initiative on methods, measurement and pain assessment in clinical trials; PedMIDAS, Pediatric migraine disability assessment scale; PCQ, Pain coping questionnaire; PCS-C, Pain catastrophizing scale-child version; RCT, Randomized controlled trial; SDQ, Strength and difficulties questionnaire; QALY, Quality adjusted life year; VAS, Visual analogue scale.
